**Measurements**

***Pulmonary function test***

Measurements of expiratory flow and inspiratory capacity will be carried out according to the ATS recommendations and performed by technicians trained in this type of tests.

***Blood samples***

A nurse, member of our research team, will take two blood samples during visit 2.

**Blood test #1 – before the EMS session:** (maximum volume = 20mL)

1. A complete blood count (4mL)
2. Inflammatory proteins and oxidative stress (12mL)
3. **CRP:** An Enzyme-Linked Immunoabsorbent Assay (ELISA) will be used to measure CRP (C Reactive Protein), an acute phase inflammatory protein.
4. **IL-6:** An Enzyme-Linked Immunoabsorbent Assay (ELISA) will be used to measure IL-6 (Interleukin-6), an inflammatory cytokine produced by muscles and found at its highest levels during muscular contraction.
5. **AOPP:** Proteins are susceptible to damage by free radicals induced by oxidative stress. AOPP (Advanced Oxidation Protein Products) is monitored in the plasma and expressed as chloramine-T equivalents by measuring the absorbance in acidic conditions at a wavelength of 340 nm in the presence of potassium iodide.

**Blood test #2 – after the EMS session:** (volume = 12mL)

Inflammatory proteins and oxidative stress (12mL)

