**Secondary objectives:**

1. To quantify the muscular fatigue induced by a session of electrical muscle stimulation in COPD patients.
2. To determine whether electrical muscle stimulation increases systemic inflammation and oxidative stress.

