**Secondary hypotheses:**

Peripheral muscular strength is reduced following electrical muscle stimulation in COPD patients (muscular fatigue).

Systemic inflammation and oxidative stress are increased after electrical muscle stimulation.

Excessive muscular fatigue and/or the increased production of inflammatory proteins could contribute to a patient’s inability to increase EMS intensity over the course of several sessions and therefore limit the effectiveness of this training modality.

1. **Protocol**

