**V2: Autonomous use of EMS, measure of pain perceived and of muscle fatigue**

The aim of this visit is to ensure that the patient can carry out electrical muscle stimulation in autonomy so that he will be able to use the apparatus at home. A full stimulation session will be carried out during which the patient will progressively take charge of the session. During electrical muscle stimulation, symptoms will be monitored (pain perception). The strength of the quadriceps will be tested before and after the session in order to measure the muscular fatigue caused by an initial EMS session. Finally, body composition will be determined during the course of this visit.

**V3: Assessment of EMS progression. Measure of pain perceived and of muscle fatigue at EMS intensity used during the sessions at home.**

The aim of this visit is to measure the pain perceived during a session of electrical muscle stimulation carried out at the EMS intensity that was used during the sessions at home. At the start of the session, the intensity of the stimulation applied will be that reached during visit 2, in order to compare the pain perceived for a given intensity, after 7 days of using the apparatus. Next, the patient will be asked to increase the intensity up to the level reached at home in order for us to calculate the intensity increase delta between V2 and V3. Throughout the course of this EMS session, the cardio-respiratory response will be measured using a portable “metabograph” fitted with a telemetric system (Oxycon mobile, Viasys). Furthermore, a blood sample will be taken before and after the session in order to measure systemic inflammation and oxidative stress levels. Lastly, muscular strength will be measured in order to determine the fatigue induced by this session.

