***Assessment of quadriceps strength and fatigue***

All measurements will be carried out on the dominant quadriceps muscle with the patient lying on his back, with the knee at a 90º angle, in a position standardised by Man et al. [21]. For the sake of the patient’s comfort, his back can be raised by an angle of 30º relative to the horizontal.

The battery of tests includes:

1. ***Maximum voluntary strength (MVS)***

Five measurements will be carried out allowing for a recovery period of 2 minutes between contractions. Measurements must be reproducible (<10% variation). The highest measurement, sustained for at least 1.5 seconds, will be used for analytical purposes. During a voluntary muscular contraction, fatigue of the rectus femoris and the vastus lateralis muscles will be objectified in real-time using surface electromyography (Biopac System) by means of electrodes placed on the skin near each muscular head. Three EMG electrodes will be placed at the heads of the quadriceps and the muscle’s electric activity will be monitored throughout the exercise.

1. ***Quadriceps twitch force (non-cooperative force) measurements***

The strength of the dominant quadriceps will also be assessed independently of the patient’s motivation during a supramaximal magnetic stimulation of the femoral nerve. This measurement will be carried out with the patient in the supine position, his knee and hip at 45º angles, as frequently performed in our lab [7]. We have previously validated this method, demonstrating its reproducibility and sensitivity to change [7].

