## TOES PROTOCOL: A STUDY OF TOLERANCE TO ELECTRICAL MUSCLE STIMULATION (EMS) IN COPD PATIENTS

[figure not shown]

**Visit 3**: 3h

- Blood sample
- Muscle strength
- **ESM training session with mobile Oxycom** (cardio-respiratory monitoring of the exercise) (30 min)
- Blood sample
- Muscle strength

**Visit 2**: 3h

- Muscle strength
- **Session to gain autonomy of use with ESM** (30 min)
- Muscle strength
- DEXA

**Visit 1**: 3h

- Consent
- Spirometry
- Fitness test (with CI)
- **EMS initiation session** (10 -15 min)

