**Objective #5**

Identify correlations between ∆Intensity (V3-V2) and the change in plasma protein content (CRP, IL-6 and AOPP) after EMS

**3. Future directions for the application and possible development of this project and potential effects on respiratory health.**

EMS is a method applicable to the rehabilitation of COPD patients but is still relatively unknown and under-employed. The investigator’s role is to supply accurate and reliable physiological data that could be used to better define patient tolerance to electrical muscular stimulation. What is more, a study such as the one described here, will allow the in-depth study of the mechanisms involved in muscular fatigue induced by EMS when performed in one of the best equipped centres with advanced understanding of the mechanisms of muscular function in COPD patients.

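### The only post-session CRP sample falls within the same 3-hour visit, so under an assumed CRP onset of 3 to 12 hours its change score cannot reflect the EMS session

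*Protocol*

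**What the plan says.** Secondary objective 2 is "To determine whether electrical muscle stimulation increases systemic inflammation and oxidative stress", and the matching hypothesis is directional: "Systemic inflammation and oxidative stress are increased after electrical muscle stimulation". The blood samples section measures CRP, IL-6 and AOPP in one sample before the EMS session and one after it. CRP is included because an ELISA "will be used to measure CRP (C Reactive Protein), an acute phase inflammatory protein". The same section describes IL-6 differently, as a cytokine that muscle produces and that is highest during contraction.

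On timing, the V3 description under Study schedule says that "a blood sample will be taken before and after the session in order to measure systemic inflammation and oxidative stress levels" and gives no clock time. It then adds "Lastly, muscular strength will be measured in order to determine the fatigue induced by this session". The visit list allots 3 hours to Visit 3, in the order blood, strength, EMS session ("cardio-respiratory monitoring of the exercise) (30 min"), blood, strength. No later sample is described.

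The change in plasma proteins is one of the criteria used for analysis, and Objective #5 correlates ∆Intensity with "the change in plasma protein content (CRP, IL-6 and AOPP) after EMS".

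The blood samples section assigns both draws to visit 2. The V3 description and the visit list assign them to Visit 3.

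**The concern.** Three markers with different roles share one before/after pair. A sample at the end of the session suits a marker that peaks during contraction. It does not obviously suit an acute-phase protein, which has to be synthesised and released before its plasma level moves.

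If the second draw comes before that can happen, the CRP change carries no information about the session, whatever EMS does. It would still be reported as one of only two inflammation markers behind secondary objective 2, and as one of three correlations in Objective #5. Marker and sampling schedule are both fixed in the protocol, so this is not a detail left to an analysis plan.

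**Working it through.** **Inputs from the protocol.** There are three severity groups of 7, and 3 × 7 = 21 patients, which reproduces the stated total. The session lasts 30 min and the visit 3 h = 180 min. For maximum voluntary strength, "Five measurements will be carried out allowing for a recovery period of 2 minutes between contractions", so one strength block takes at least 4 × 2 = 8 min.

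**Assumptions, not in the documents.** CRP onset 3 to 12 h after the stimulus; CRP half-life 19 h (range 12 to 24 h); assay CV 5% to 10%; plasma-volume fall during the session 0% to 10%, with a between-patient SD of 3% when a fall is present.

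**Step 1: when is the second draw?**
- As listed: about 30 min after EMS starts.
- Latest time if the listed order is kept: one strength block precedes EMS and one follows the draw, so 180 − 8 − 8 = 164 min after EMS starts, or 164 − 30 = 134 min after it ends. This allows no time for the first blood draw, the twitch test or set-up, so it is generous.
- If the blood belongs to Visit 2, which also lasts 3 h, the draw still cannot fall later than 180 min after EMS starts.

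**Step 2: is an assumed onset reached by 164 min (2.7 h)?**

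| Assumed onset | Reached? |
|---|---|
| 2 h | yes |
| 3 h | no |
| 4 h | no |
| 6 h | no |
| 8 h | no |
| 12 h | no |

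Only an onset of about 2.7 h or less would fit.

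**Step 3: does the result depend on the lag?** Suppose there were no lag and synthesis rose S-fold at the first pulse. The fractional rise would be (S − 1)(1 − 2^(−t/T)).

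| S | t | T = 24 h | T = 19 h | T = 12 h |
|---|---|---|---|---|
| 2 | 30 min | 1.4% | 1.8% | 2.9% |
| 2 | 45 min | 2.1% | 2.7% | 4.2% |
| 2 | 164 min | 7.6% | 9.5% | 14.6% |

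With S = 10, T = 19 h and 45 min, the rise is 9 × 2.7% = 24%. Slow turnover alone therefore does not settle the matter. The lag does.

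**Step 4: what is left if no CRP is released?**
- SD of an individual change = √2 × CV: 7.1% at CV 5%, 14.1% at CV 10%.
- Standard error of the mean change in 21 patients = SD/√21: 1.5% and 3.1%.
- A plasma-volume fall of fraction f raises the concentration by 1/(1 − f) − 1. Simulated paired t-tests (n = 21, 20,000 runs, zero true release) gave:

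| Fall | Apparent mean rise | p < 0.05, CV 5% | p < 0.05, CV 10% |
|---|---|---|---|
| 0% | 0% | 5% | 5% |
| 2% | 2% | 21% | 9% |
| 5% | 5% | 83% | 34% |
| 10% | 11% | >99% | 89% |

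No plasma-volume correction is described. The complete blood count appears only in blood test #1, so there is no paired count from which a shift could be estimated.

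**Step 5: the Objective #5 correlation.** With n = 21, pure noise gives r within about ±0.44 in 95% of samples. By Fisher's z, 80% power needs |r| = tanh[(1.96 + 0.84)/√18] ≈ 0.58. A CRP change made of measurement error would give a correlation that cannot be interpreted.

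**The case against.** The strongest objection is that the decisive premise is not in the documents. The protocol calls CRP an acute-phase protein and gives no kinetics. Without a lag, a doubling of synthesis gives 7.6% to 14.6% by 164 min. Against a standard error of 1.5% to 3.1%, a mean shift of that size could be seen in 21 patients. Comparing a small rise with a single-assay CV is also the wrong yardstick for a group mean; it matters for the individual changes in Objective #5. All of this stands, so the conclusion has to rest on the stated onset range.

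A reader might infer three stronger things that the documents do not support:
- **That the second draw is immediate.** The prose says only that it is taken after the session. Immediacy is inferred from the order in the visit list. The argument therefore uses the latest time the visit allows.
- **That a null is certain and will be misread as no inflammation.** No section says how a CRP null would be interpreted. IL-6 is measured in the same samples and is the marker the protocol ties to contraction. An uncorrected plasma-volume fall could also produce a false increase.
- **That CRP has no use here.** If the blood is taken at V3, the pre-session level could carry an effect of the five home sessions. Only the change score across the session is in question.

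It is also fair that the tolerance, pain, body composition, cardio-respiratory and fatigue analyses are untouched.

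**Conclusion.** The point holds for the CRP change score, conditionally on an onset of 3 h or more. The second draw falls about 30 min after EMS starts as listed, and at most about 164 min after it in the listed order. No assumed onset from 3 to 12 h is reached, so the CRP part of secondary objective 2 and of Objective #5 cannot answer its question. What remains is assay error (individual SD 7% to 14% at an assumed CV of 5% to 10%) and any plasma-volume shift, which can mislead in either direction. If onset were about 2.7 h or less and the draw were delayed to the end of the visit, the conclusion would weaken.

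The evidence does not reach secondary objective 2 as a whole, since IL-6 and AOPP remain. Severity is minor to moderate.

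**What to change.** 1. Remove CRP from blood test #2, from the plasma-protein criterion under Criteria used for analysis, and from the change analysis in Objective #5.
2. Test the acute inflammatory response on IL-6, with AOPP for oxidative stress, and state that secondary objective 2 covers the immediate response only.
3. Keep pre-session CRP and relate it to ∆Intensity as a level, not as a change.
4. Reconcile the blood samples section (visit 2) with the V3 description and the visit list (Visit 3). If the blood is at V3, do not call the pre-session CRP a baseline, because it follows the five home sessions.
5. State the time of the second draw in minutes after the end of the session. A blood count in that sample as well would allow a plasma-volume correction for IL-6 and AOPP.

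Items 1 to 4 cost wording and save 21 CRP assays, one per patient. The count in item 5 adds 4 mL of blood, going by the volume given for blood test #1. The downside is that the acute inflammation result then rests on one marker, which under the assumed onset is already so. The alternative is a later CRP sample, which keeps the marker but needs an attendance beyond the 3-hour visit.

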1. CRP
2. IL-6
3. AOPP

Blood will be centrifuged in order to separate the plasma and will be conserved at -80°C for subsequent analyses. If the patient accepts and signs the “Banque de Tissus Pneumologie” (Pulmonology Tissue Bank) form, the remaining blood will be banked.

***Pain perception***

Pain perception will be measured using a visual analogue scale (VAS) with one non-graduated side (for the patient) and one graduated side (for the investigator) used to put a number on the measure.

***Assessment of body composition using DEXA***

Body composition will be assessed using DEXA which allows the local quantification of bone density, lean body mass and body fat. This measure will allow us to determine the regional distribution of lean body mass vs body fat.

***Assessment of quadriceps strength and fatigue***

All measurements will be carried out on the dominant quadriceps muscle with the patient lying on his back, with the knee at a 90º angle, in a position standardised by Man et al. [21]. For the sake of the patient’s comfort, his back can be raised by an angle of 30º relative to the horizontal.

The battery of tests includes:

1. ***Maximum voluntary strength (MVS)***

Five measurements will be carried out allowing for a recovery period of 2 minutes between contractions. Measurements must be reproducible (<10% variation). The highest measurement, sustained for at least 1.5 seconds, will be used for analytical purposes. During a voluntary muscular contraction, fatigue of the rectus femoris and the vastus lateralis muscles will be objectified in real-time using surface electromyography (Biopac System) by means of electrodes placed on the skin near each muscular head. Three EMG electrodes will be placed at the heads of the quadriceps and the muscle’s electric activity will be monitored throughout the exercise.

1. ***Quadriceps twitch force (non-cooperative force) measurements***

The strength of the dominant quadriceps will also be assessed independently of the patient’s motivation during a supramaximal magnetic stimulation of the femoral nerve. This measurement will be carried out with the patient in the supine position, his knee and hip at 45º angles, as frequently performed in our lab [7]. We have previously validated this method, demonstrating its reproducibility and sensitivity to change [7].

***Bleep fitness test***

In order to quantify the patient’s cardio-respiratory response to maximum effort, patients will undergo an incremental bleep fitness test as frequently carried out in our lab (Pepin et al. 2005). This test uses a portable “metabograph” fitted with a telemetric system (Oxycon mobile, Viasys) to measure ventilation, oxygen consumption, heart rate and saturation throughout the exercise. Physiological values measured during a session of electrical muscle stimulation can therefore be compared to the maximal values measured during this test. Furthermore, this test will allow us to characterise the patients’ physical condition. Fifteen minutes before this test an electrocardiogram (ECG) at rest will be carried out.

## TOES PROTOCOL: A STUDY OF TOLERANCE TO ELECTRICAL MUSCLE STIMULATION (EMS) IN COPD PATIENTS

[figure not shown]

**Visit 3**: 3h

- Blood sample
- Muscle strength
- **ESM training session with mobile Oxycom** (cardio-respiratory monitoring of the exercise) (30 min)
- Blood sample
- Muscle strength

**Visit 2**: 3h

- Muscle strength
- **Session to gain autonomy of use with ESM** (30 min)
- Muscle strength
- DEXA

**Visit 1**: 3h

- Consent
- Spirometry
- Fitness test (with CI)
- **EMS initiation session** (10 -15 min)

**ESM at home**

5 sessions carried out in autonomy

Contact by phone

D0 + 8

D0 + 1

D0

**Details of the electrical muscle stimulation sessions**

General concept: Simultaneous muscular stimulation of both legs induced by an electric current conducted by two cutaneous electrodes. Throughout the session, a period of muscular contraction alternates with an “active” recovery period (stimulation frequency which favours local blood circulation). The stimulation intensity is progressively increased provided it is well tolerated by the patient.

Site: LAVAL hospital and at the patient’s home

**Visit 1: Initiation session:** presentation of the electrical muscle stimulation program, positioning of the electrodes and learning how to use the apparatus.

**Visit 2: Session to gain autonomy of use:** observation that the patient can satisfactorily carry out an EMS session autonomously.

**At home: five EMS sessions carried out autonomously at home**

During the seven days separating visits V2 and V3, the patient will be required to carry out 5 sessions at home. He will be asked to increase the EMS intensity as much as he can throughout one session and from one session to another, whilst staying beneath his pain threshold. In other words, he will have to increase the intensity frequently in order to always be at the maximum bearable intensity. For each session, the patient will have to write down the initial and final intensities along with the level of pain perceived for each. Throughout the week, we will maintain contact by phone (one initial phone call the day of the first session at home and then according to the patient’s needs) in order to answer any questions and/or solve any potential technical difficulties.

**Visit 3: Training session,** session as carried out by the patient at home.

Electrode placement

**Three electrodes on each leg:** two electrodes (50*50 mm) are placed on the skin by the lateral and the medial vastus of the quadriceps + one electrode (50*90 mm, double outlet) placed horizontally towards the top of the thigh, beneath the groin.

**
[figure not shown]

[figure not shown]
**

*Electrode placement for thigh rehabilitation*

*In this picture, the electrodes placed at the upper thigh are smaller models which will be replaced by electrodes of larger calibre, positioned side by side lengthwise (59*90 mm)*

**Electrode placement will be standardised** so as to lie by the lateral and the medial vastus motor points. The motor points will be identified for each patient individually, using a **pen electrode** that helps determine motor pathways and points of emergence.

Program

**Intermittent frequencies**: contraction at 50 Hz / “active” muscle relaxation at 5 Hz

- - - contraction 7 sec / relaxation 10 sec

**Time to reach contraction**: 3 seconds / time to relaxation: 1 second. Considering that the contraction is incomplete during the first two seconds of the contraction process, the cycles are 30%.

**Pulse width** = 400 µm

**The intensity** at which the patient begins to feel contraction of his thigh muscle is defined as the initial intensity; it is then progressively increased in order to reach the maximal bearable intensity.

**Patient recruitment**

The host laboratory (Laval Hospital) is a research centre that ensures a regular recruitment of patients to clinical research projects.

**Electrical muscle stimulation implementation**

The use of electrical muscle stimulation as a home-based rehabilitation protocol is currently under investigation as part of the ESTIM protocol (CER # 20105). The main purpose of this protocol is to describe patient tolerance to EMS (symptoms with effort) and the physiological effects induced by an EMS training session in the context of a rehabilitation program (during the 7^th^ session). In this protocol, electrical muscle stimulation is first used at the hospital, subsequently performed at home in five sessions spread over seven days, and finally used to assess the patient during a seventh personalised session.

**Criteria used for analysis**

- Tolerance to EMS: pain perceived for a given stimulation intensity and the increase in intensity between sessions V2 and V3, ie. ∆Intensity (V3-V2)

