**Hypotheses:**

**Main hypothesis:**

Some COPD patients have a low tolerance to electrical muscle stimulation (small or null increase in intensity after 5 sessions).

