**Objective #2**

Identify correlations between ∆Intensity (V3-V2) and the pain perceived during the initial session V2 (VAS reading for the intensity reached during V2) and between ∆I (V3-V2) and the change in pain perceived between V2 and V3 (VAS reading at equal intensity)

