**Objective #3**

Identify correlations between ∆Intensity (V3-V2) and body composition around the quadriceps

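### Objective 2 correlates raw ∆Intensity (V3-V2) with a pain score read at each patient's own V2 intensity, so V2 intensity enters both sides and should be a covariate in that analysis

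*Protocol*

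**What the plan says.** The section on criteria used for analysis gives tolerance two parts. One is pain scored at a fixed intensity; the other is "the increase in intensity between sessions V2 and V3, ie. ∆Intensity (V3-V2". The main hypothesis describes low tolerance as a "small or null increase in intensity after 5 sessions", without reference to the starting level and without a numerical cut-off. The V3 visit description explains how the difference is obtained: the session starts at the intensity reached at V2, and the patient's next task is described as follows: "increase the intensity up to the level reached at home in order for us to calculate the intensity increase delta between V2 and V3".

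All five analysis objectives take this raw difference as the variable to be explained. The first predictor in Objective 2 is "the pain perceived during the initial session V2 (VAS reading for the intensity reached during V2". Objective 3 reads "Identify correlations between ∆Intensity (V3-V2) and body composition around the quadriceps". The analysis section mentions simple and multiple regressions but names no covariates, and V2 intensity is not listed as one anywhere.

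The programme details say of the stimulation intensity that "it is then progressively increased in order to reach the maximal bearable intensity". V2 is a full session, so patients may differ widely in how close to their limit they already are when the starting value is taken.

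**The concern.** In the first Objective 2 correlation, V2 intensity does two jobs. It enters the outcome with a minus sign, and it fixes the current at which pain is scored. Two patients with the same pain sensitivity can therefore have different pain scores and different values of ∆Intensity only because one pushed further at V2. A patient who went high at V2 may report more pain and have less room to rise; a cautious patient may report less pain and have more room. The plan would read the resulting correlation as an effect of pain on tolerance, which is the specific hypothesis being examined.

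The same feature affects how individual patients are described. One who reaches a high intensity at V2 and holds it has a ∆Intensity near zero, as does one who starts low and stays low. The difference alone cannot tell them apart.

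**Working it through.** **Inputs.** The only design figure in the protocol is the sample size: 3 groups × 7 = 21, which reproduces. No SD of intensity, V2-V3 correlation, alpha or power is stated. The following are therefore assumptions, shown as ranges: ρ = corr(V2, V3) from 0.5 to 0.9; k = SD(V3)/SD(V2) of 0.8, 1 or 1.25; and a two-sided 5% test.

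**Step 1: coupling of ∆Intensity with V2 intensity.** With SD(V2) = 1,

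corr(∆, V2) = (ρk - 1) / √(1 + k² - 2ρk).

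For k = 1 this reduces to -√((1 - ρ)/2). For example, ρ = 0.5 gives -√0.25 = -0.50.

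| k | ρ = 0.5 | ρ = 0.7 | ρ = 0.8 | ρ = 0.9 |
|---|---|---|---|---|
| 0.8 | -0.65 | -0.61 | -0.60 | -0.63 |
| 1 | -0.50 | -0.39 | -0.32 | -0.22 |
| 1.25 | -0.33 | -0.14 | 0.00 | +0.22 |

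The coupling is negative when ρk < 1, zero when ρk = 1 and positive above that.

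**Step 2: what a predictor inherits.** A predictor related to intensity only through V2, with correlation r to V2 intensity, correlates r × corr(∆, V2) with the outcome. At k = 1 and r = 0.6 this is 0.6 × (-0.50, -0.39, -0.22) = -0.30, -0.23, -0.13 for ρ = 0.5, 0.7, 0.9. If r is negative, the signs reverse.

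**Step 3: consequence at n = 21.** The critical |r| is 0.433. In a simulation of 40,000 replicates per scenario, a predictor linked only to V2 intensity (r = 0.5 to 0.9) was declared significant against raw ∆Intensity in 8% to 56% of trials at k = 1 and in 5% to 26% at k = 1.25. With V2 intensity in the model the rate was about 5% in every scenario. That result holds for predictors tied solely to V2 intensity and for V2 intensity recorded without error. With error in V2 intensity, adjustment removes the artefact only in part.

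**Step 4: predictors measured in the V3 session.** Take a predictor correlated 0.6 with V3 intensity and otherwise unrelated to V2, with k = 1.

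- Unadjusted: 0.6 × √((1 - ρ)/2) = +0.30, +0.23, +0.13 for ρ = 0.5, 0.7, 0.9.
- Adjusted for V2 intensity: 0.6√(1 - ρ²) / √(1 - 0.36ρ²). At ρ = 0.5 this is 0.520/0.954 = +0.54; at 0.7, 0.428/0.908 = +0.47; at 0.9, 0.262/0.842 = +0.31.

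Here V2 adjustment makes the coupling stronger.

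**The case against.** The strongest reply is that change is the construct the protocol intends. Its overall objective defines tolerance as the ability to raise intensity, and the introduction explains that patients who cannot do so gain less from treatment. The plan also lists pain at a given intensity as a tolerance criterion, starts V3 at the V2 intensity, and allows multiple regressions, whose covariates an analysis plan could name. This justifies keeping ∆Intensity as the outcome. It does not repair the V2-pain correlation: pain at a given intensity is not the outcome of any objective, and the V2 score is read at a different current in each patient.

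The second reply is that the mechanism is assumed. If all patients stop at their bearable limit, V2 pain may be similar across currents. If pain-sensitive patients stop early, pain and V2 intensity correlate negatively, and under equal SDs the artefact would oppose the hypothesis. Spread may also grow over five home sessions. All of this stands: neither size nor sign can be fixed from the document.

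Three stronger readings are tempting and unsupported.

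- *Objectives 2 and 3 would appear confirmed by artefact.* For Objective 2 the sign is undetermined. For Objective 3 the protocol expects low thigh fat to go with lower tolerance, hence a positive fat-∆Intensity correlation. If thinner patients reach lower V2 intensities, a negative coupling works against that hypothesis.
- *Patients high at V2 are scored intolerant.* There is no cut-off, and ∆Intensity is analysed as a continuous variable.
- *V2 intensity belongs in every model.* Step 4 shows that this worsens the coupling for predictors tied to V3 intensity.

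**Conclusion.** The point holds for the V2-pain analysis in Objective 2. The protocol fixes a raw difference as outcome and a predictor read at the very value being subtracted, so the correlation cannot separate pain sensitivity from how far the patient had gone at V2. Corr(∆, V2) is -0.50 to -0.22 under equal SDs and -0.33 to +0.22 if the SD grows by 25%, over assumed V2-V3 correlations of 0.5 to 0.9. The problem is negligible only if ρk is close to 1 or V2 pain is unrelated to V2 intensity, and the document gives no ground for relying on either.

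For Objective 3 the case is weaker. The introduction says body composition may alter current transmission, so it may itself affect V2 intensity, and conditioning on V2 intensity then changes the question asked. Neither the adjusted nor the unadjusted model is plainly the right one.

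For predictors measured in the V3 session the point does not carry over. This is a worthwhile correction to one analysis and to the reporting, not a defect in all five objectives.

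**What to change.** 1. **Objective 2, V2 pain.** Regress ∆Intensity (or V3 intensity) on V2 pain with V2 intensity as a covariate. The pain coefficient is the same for either outcome and reads as pain at a given V2 intensity, in line with the protocol's own criterion. The unadjusted correlation can be reported as secondary.
2. **Objective 3.** Report the V2-adjusted model beside the unadjusted one as a sensitivity analysis, and state that body composition may itself affect V2 intensity.
3. **Predictors measured in the V3 session.** Do not present V2 adjustment as a remedy for the cardio-respiratory response (Objective 1) or for the V3 fatigue and blood measures (Objectives 4 and 5). Note instead that they are coupled with V3 intensity. The visit description and flow chart place the blood samples at V3 while the blood samples section places them at V2, so that must be reconciled first.
4. **Reporting.** Show each patient's V2 and V3 intensities beside ∆Intensity before describing a small increase as low tolerance.

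The cost is a few sentences in the analysis section and one degree of freedom among 21 patients. The V2 intensity is already needed to compute ∆Intensity, so no new data are required.
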